### Procedure

#### Pre-intervention (baseline) phase

This phase will consist of the usual care that the patients in the inpatient wards receive and will last for 6 weeks (see table 1). We will assess this current practice by conducting interviews and by inspecting current documentation sheets. These will be completed by one on-site research practitioner. We will perform individual online interviews with the patients, mental health professionals and carers (relatives) to assess the degree of the satisfaction of the patients and carers as well as their views/thoughts regarding their current discharge plans. At the end of this phase, patients will be asked to complete a series of study questionnaires, including the Evaluating and Quantifying User and Carer Involvement in Mental Health Care Planning Patient‐Reported Outcome Measure (EQUIP-PROM) Scale,^23^ which measures the involvement of both the patients and carers in healthcare planning during/after discharge, the Care Transitions Measure (CTM)^24^ and a five-item patient-centred scale focusing on mental health discharge outcomes that were identified as important to patients in previous work.^9^ Patients, carers and professionals will also be invited to be interviewed about their experiences of usual care, via the study information pack.

**Table 1 T1:** Data collection procedures

Baseline phase (6 weeks)	Training phase (2 weeks)	Intervention phase (2 weeks)
Patient/carer outcome measures (n=45): EQUIP-PROM Scale 5 items regarding general satisfaction about discharge planning Interviews with professionals, carers and patients	Training evaluation questionnaires	Patient/carer outcome measures (n=45): EQUIP-PROM Scale 5 items regarding general satisfaction Care Transitions Measure Staff outcome measures (n=45): AIM IAM FIM Adherence to the delivery of the SAFER patient flow bundle will be measured Interviews with professionals, carers and patients

AIM, Acceptability of Intervention Measure; EQUIP-PROM, Evaluating and Quantifying User and Carer Involvement in Mental Health Care Planning Patient‐Reported Outcome Measure; FIM, Feasibility of Intervention Measure; IAM, Intervention Appropriateness Measure.

### Training phase

The training will be a series of self-led short videos and self-help manuals to the pilot ward staff participating in the study. This phase will last for 2 weeks. We aim to use evaluation questionnaires following the training. Interviews in the training phase will explore whether the interventions have been fully comprehended by staff and ensure that we have enough time to solve any problems regarding the training as they arise.

### Intervention phase

This phase will last for 6 weeks during which the wards will receive the SAFER-MH and SAFER-YMH patient flow bundle (figure 1). Data regarding the adherence of the mental health professionals to using the SAFER-MH bundle will be collected. Individual online interviews (Zoom) will be conducted with patients and carers (within 3 months after discharge) and with mental health professionals (within 1 month after the completion of the 6-week intervention phase) to assess the feasibility and acceptability of the SAFER-MH bundle. Each patient/carer will only be interviewed once; professionals may be interviewed more than once in different stages of the project. At the end of this 6-week phase, patients will be asked to complete the same study scales that were administered during the baseline and which were completed by a different pool of patient participants discharged at the time. We will also administer the three staff outcome measures after the intervention phase is complete.

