## Introduction

It is estimated that 1 in 4 adults and 1 in 10 children will be affected by mental or neurological disorders at some point in their lives.^1 2^ Mental illness has become the single largest cause of disability in England, costing the National Health Service (NHS) over £13.3 billion in 2019/2020 alone and is rising among both children and adults.^3–5^ Individuals who are admitted to inpatient mental health services are at higher risk of adverse outcomes such as shorter life expectancy; increased risk of homelessness; self-harm, violence and criminal activity; and increased likelihood of many other adverse psychosocial outcomes, including loneliness, isolation and stigma.^6–10^

Transitions into and out of acute psychiatric hospitals are risky stages in the healthcare pathway associated with patient safety issues. The absence of continuity of care is an important risk factor for patient safety incidents during transitions of care.^8^ Other patient safety risk factors may include: difficulties of medication management across the care system; delayed discharge often arising from insufficient housing, social or community care provision; and lack of information sharing between services (primarily between primary and secondary care).^6 10–14^

Multifaceted interventions have been increasingly used to improve patient safety and reduce readmissions in complex care transitions.^11 14–17^ The SAFER patient flow bundle is an exemplar multifaceted intervention, developed by NHS England/Improvement to improve discharge from acute hospitals to the community.^18^ The SAFER patient flow bundle consists of five components: (1) senior review (before midday); (2) expected discharge date and clinical criteria for discharge; (3) early assessments to improve patient flow; (4) early discharge (aiming to discharge patients before midday) and (5) a multidisciplinary review for patients with increased length of stay.^18^ Many of the individual components of the SAFER bundle are used as standard practice or best practice guidelines in policy.^19^ Preliminary evidence obtained by case studies across the country is promising as it shows that SAFER has resulted in reduced length of patient stay in different hospitals, diminished discharge delays with minimal complications and decreased readmissions or contact with primary care. Furthermore, patient and staff satisfaction have increased.^20^

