### Participants

All patients admitted to pilot wards during the study period (14 weeks from November 2022 onwards) will receive the intervention, as it is a best practice intervention delivered as a service improvement change in care. Each individual participant who is due to be discharged from the pilot ward will then be given the option to consent (parental/guardian consent for under 16 years) whether to be a participant in the research studies by participating in the interviews and by completing relevant questionnaires. Patient participants will be adults (phase 1) or young people (phase 2) with mental illness who were admitted to an inpatient ward. Healthcare professionals who will be delivering the intervention and carers/family members of the patients (who consent to be involved) will also be involved in the interview components of the study (patient and carer interviewees can decide whether to be interviewed alone or together).

We will collect data from all consenting patients who are discharged during the baseline and intervention stages, irrespective of whether their inpatient stay began before this period. In the case of an unplanned or early discharge, we will still collect data from consenting patients who have received the intervention; if a patient is not discharged from the pilot ward (due to transfer, etc), they will be ineligible to participate.

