### Carer/parent/guardian participants

A study pack will be handed to each patient at discharge; this will include a carer pack, which they can choose to pass on or discard. The pack will include details of the study, paper questionnaires and a paper consent-to-contact form for interviews, as well as an online link to assess the documents remotely. For patients who agree to be contacted for an interview, we will ask again if they would like to share the information pack and contact details with their informal carer when contacted.

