### Quantitative outcomes

These will be measured in the baseline phase and intervention phase with different patients. To assess patients’ and carers’ perspectives, the quantitative outcomes will be measured using paper/online versions of a series of questionnaires which include: (1) the EQUIP-PROM, a 14-item co-designed measure to assess patient/carer views of care planning in mental health,^23^ (2) a short four-item version of the CTM^24^ and (3) the five novel items assessing the safety of mental healthcare transitions^9^; properties of these outcome measures can be found in table 2.

**Table 2 T2:** Properties of outcome measures used

Validated outcome measure	Psychometric properties	Scoring system
EQUIP	Scale has acceptable scalability (Ho=0.69), reliability (alpha=0.92), fit to the Rasch model (χ2(70)=97.25, p=0.02), and no differential item functioning or locally dependent items.	It uses a 5-point Likert scale ranging from 1=‘strongly disagree’ to 5=‘strongly agree’, with a middle neutral value meaning ‘neither agree nor disagree’. Higher scores indicate higher-perceived quality care planning.
CTM-4	The Cronbach’s alpha for CTM-4 is 0.85.	The CTM items are rated on a 4-point Likert scale ranging from 1=‘strongly disagree’ to 4=‘strongly agree’, with a fifth response being ‘don’t know/don’t remember/not applicable’. The summarised score (excluding the ‘not applicable’ scores) is computed as the total sum divided with the number of answered items, minus 1 and multiplied by 100 to get a total score (0–100) for each respondent. Higher scores indicate better patient/carer experience of care transitions.

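### Patient and carer interviews, the only described source of their views on the bundle, are stated as online with no alternative mode, so people with poor digital access or privacy may be under-represented

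*Protocol article*

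**What the plan says.** Under Intervention phase, the protocol article states: "Individual online interviews (Zoom) will be conducted with patients and carers (within 3 months after discharge". Under Pre-intervention (baseline) phase it states: "We will perform individual online interviews with the patients, mental health professionals and carers (relatives". Zoom is named only in the first of these. The baseline section says of the interviews and the inspection of documentation: "These will be completed by one on-site research practitioner". The one choice offered to interviewees, under Participants, concerns company and not mode: "patient and carer interviewees can decide whether to be interviewed alone or together".

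Questionnaires are treated differently. Under Quantitative outcomes, "the quantitative outcomes will be measured using paper/online versions of a series of questionnaires". The carer pack contains "paper questionnaires and a paper consent-to-contact form for interviews, as well as an online link".

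The three staff scales (acceptability, appropriateness, feasibility) are for professionals and are given after the intervention phase only. Under Outcomes, the main focus of the evaluation is whether the bundle is acceptable and for which people.

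**The concern.** Acceptability to patients and carers is part of the first primary objective. If the only instrument that can ask them about the bundle is reached through a device, a data connection and a private place, then those who lack these are less likely to be heard. The article gives its own grounds for taking this seriously. The Introduction describes people admitted to inpatient mental health services as having "increased risk of homelessness", along with loneliness and isolation, and lists insufficient housing among the causes of delayed discharge. Interviews may also fall up to three months after discharge, when help from ward staff can no longer be assumed.

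What is at stake is the subgroup part of the question. A sample that under-represents people with poor access cannot say much about whether the bundle suits them, and that answer is meant to inform the design of a main trial.

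**Working it through.** The article states no figure on this point, so there is none to reproduce. The check is a reading of the relevant sections side by side, followed by one illustrative calculation.

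**Step 1. Is another interview mode stated?** Baseline: online. Intervention phase: online, by Zoom. The only mention of meeting in person or remotely, under Inpatient mental health ward sites, concerns the study team's meetings with services. No telephone or in-person option for interviewees appears in the article.

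**Step 2. Does another source ask patients and carers about the bundle?**

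| Source | Who completes it | What it asks about |
|---|---|---|
| Acceptability, appropriateness and feasibility scales | Professionals, after the intervention phase | The bundle |
| Adherence self-report form | Concerns delivery by professionals | Delivery of the bundle |
| EQUIP-PROM | Patients and carers | Care planning |
| Four-item Care Transitions Measure | Patients and carers | Experience of the transition |
| Five novel items | Patients and carers | Safety of, and satisfaction with, discharge |
| Interviews, intervention phase | Patients, carers, professionals | Feasibility and acceptability of the bundle |

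The text of the Intervention phase section says the patient scales are those already used at baseline, when the bundle is not yet in place, so they are not scales about the bundle. Table 1 lists the Care Transitions Measure under the intervention phase only. Even so, its subject is the transition and not the bundle. The interviews are the one remaining source.

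**Step 3. Who enters the interview pool?** Under In-depth qualitative outcome data, interviewees are volunteers among those who complete questionnaires. Access to a video call is a further filter after questionnaire completion and willingness.

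**Step 4. What is the right base for an illustration?** Table 1 gives n=45 patient/carer respondents at baseline and n=45 in the intervention phase. These add to 45 + 45 = 90, the phase 1 target in the Data analysis plan. Baseline interviews concern usual care, so only the intervention-phase 45 can judge the bundle.

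**Step 5. Illustration.** The share without usable online access is not in the article. Assume a share *p* of 10% to 30%; the number affected is *p* × 45:

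- 0.10 × 45 = 4.5, about 5
- 0.30 × 45 = 13.5, about 14

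The 45 is a questionnaire target. No interview target is stated, so these figures show how many people might find the stated mode hard to use. They do not count interviews lost. The phase 2 target of 40 is not split by period, so no matching figure is given for young people.

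**The case against.** The strongest reply is that the article never says interviews are online *only*, sets no digital-access criterion, and offers an interview to everyone who completes the questionnaires. It condenses a fuller protocol, in which a telephone option may be written down. The on-site practitioner leaves room for assisted access at baseline, and a patient may be interviewed together with a carer who has a device. The Data analysis plan will also report interviews completed against patients discharged, so overall non-participation will be visible.

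Much of this stands, and it limits the point. A reader might infer that people without online access are *excluded*. The text does not support that; under-representation is a possibility and not a stated rule. A reader might also infer that the acceptability finding is tilted upward, because those with the hardest discharges are the hardest to reach. That is plausible, but the article says nothing about online access in this population or about how those without it view the bundle. Finally, applying the assumed 10–30% to all 90 phase 1 respondents, giving 9–27, would wrongly include baseline respondents who never experienced the bundle.

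The reply does not remove the point. The mode is a stated method in two sections, not an omitted detail. Assistance on site at baseline does not clearly help someone contacted after discharge. Joining with a carer does not help a patient who has none involved, or who wants to speak privately. The planned reporting shows how many did not take part, but not by mode or because of mode.

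**Conclusion.** The point holds as a matter of possible under-representation. Online is the only mode stated for patient and carer interviews in both phases. Those interviews are the only described source of patients' and carers' views on the bundle, and the study's main question includes for whom the bundle is acceptable.

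The size and direction of any resulting bias cannot be derived from the article. The figure of about 5–14 of 45 rests entirely on the assumed access range and on the Table 1 target being met. The conclusion does not depend on it. If the full protocol already offers another mode, what remains is to say so and to record which mode was used. This is a cheap improvement to a feasibility study and does not threaten the rest of the design.

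**What to change.** In the Pre-intervention (baseline) phase and Intervention phase sections, replace *online interviews* and *online interviews (Zoom)* with *interviews by video or telephone, as the participant chooses*. Keep the post-discharge timing stated for the intervention phase, and use the same topic guide for both modes. Record the mode of each interview and, where given, the reason for declining, and report both by phase.

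Interviewing patients on the ward before discharge is not a suitable alternative. It would depart from the post-discharge timing and could come before the discharge tasks, namely co-producing the written plan and making sure the patient has a copy. Those are among the parts of the bundle on which patients' views are wanted.

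The cost is small: a wording change and probably a minor ethics notification. Telephone loses visual cues, and mode has to be noted in the qualitative analysis.

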**Figure 1 F1:**
[figure not shown]
Timeline of events.

### Outcomes

The aim of the evaluation will be to determine the feasibility and acceptability of the SAFER-MH and SAFER-YMH interventions by patients, carers and professionals. Additionally, we aim to identify the completion rates and if there are any changes in the key outcomes. As this is a pre/post uncontrolled feasibility study, it will only give us a first indication about the appropriateness of the outcome measures whereas we will primarily focus on whether the SAFER-MH and SAFER-YMH is acceptable and, if so, for whom. We chose 6-week phases, as studies in UK settings indicate average adult length of stays at around 22–36 days and the NHS Mental Health Implementation Plan aims to reduce length of inpatient psychiatric stays to a maximum of 32 days, enabling us to capture a considerable number of patients during the study.^25 26^

### Quantitative outcomes

These will be measured in the baseline phase and intervention phase with different patients. To assess patients’ and carers’ perspectives, the quantitative outcomes will be measured using paper/online versions of a series of questionnaires which include: (1) the EQUIP-PROM, a 14-item co-designed measure to assess patient/carer views of care planning in mental health,^23^ (2) a short four-item version of the CTM^24^ and (3) the five novel items assessing the safety of mental healthcare transitions^9^; properties of these outcome measures can be found in table 2.

**Table 2 T2:** Properties of outcome measures used

Validated outcome measure	Psychometric properties	Scoring system
EQUIP	Scale has acceptable scalability (Ho=0.69), reliability (alpha=0.92), fit to the Rasch model (χ2(70)=97.25, p=0.02), and no differential item functioning or locally dependent items.	It uses a 5-point Likert scale ranging from 1=‘strongly disagree’ to 5=‘strongly agree’, with a middle neutral value meaning ‘neither agree nor disagree’. Higher scores indicate higher-perceived quality care planning.
CTM-4	The Cronbach’s alpha for CTM-4 is 0.85.	The CTM items are rated on a 4-point Likert scale ranging from 1=‘strongly disagree’ to 4=‘strongly agree’, with a fifth response being ‘don’t know/don’t remember/not applicable’. The summarised score (excluding the ‘not applicable’ scores) is computed as the total sum divided with the number of answered items, minus 1 and multiplied by 100 to get a total score (0–100) for each respondent. Higher scores indicate better patient/carer experience of care transitions.
AIM, FIM, IAM	The alphas for 5-item scales were between 0.87 and 0.89. Scale refinement based on measure-specific Confirmatory Factor Analyses (CFAs) and Cronbach’s alphas using vignette data produced 4-item scales (alphas from 0.85 to 0.91). A three-factor CFA exhibited acceptable fit (Comparative fit index (CFI)=0.96, Root Mean Square Error of Approximation (RMSEA)=0.08) and high factor loadings (0.75–0.89), indicating structural validity. ANOVA showed significant main effects, indicating known-groups validity. Test–retest reliability coefficients ranged from 0.73 to 0.88.	1=completely disagree, 2=disagree, 3=neither agree nor disagree, 4=agree, 5=completely agree. Scoring instructions: scales can be created for each measure by averaging responses. Scale values range from 1 to 5. Higher scores indicate higher acceptability, appropriateness and feasibility of the intervention.

AIM, Acceptability of Intervention Measure; ANOVA, analysis of variance; CTM-4, four-item version of the Care Transitions Measure; EQUIP, Evaluating and Quantifying User and Carer Involvement in Mental Health Care Planning; FIM, Feasibility of Intervention Measure; IAM, Intervention Appropriateness Measure.

To assess professionals’ perspectives, we will use three measures: the Acceptability of Intervention Measure, Intervention Appropriateness Measure and Feasibility of Intervention Measure. Each of the three measures contains four items to assess professionals’ perspectives on a new intervention. These measures will be administered after the intervention phase only (not the baseline). Adherence to the delivery of the SAFER-MH and SAFER-YMH bundle will be measured using a purposefully designed self-report form, and recruitment rates will be recorded at each stage.

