### Data analysis plan

We will be following the published extension to Consolidated Standards of Reporting Trials (CONSORT)^27^ when reporting the results of this feasibility study. As this is a feasibility study, no formal sample size calculation has been conducted. Our targeted sample size (n=90, phase 1; n=40, phase 2) should be large enough to consider the practicalities of recruitment and delivering the interventions.

Descriptive statistics for intervention feasibility, acceptability and appropriateness will be presented. A chart of participant flow during the whole study will be plotted (CONSORT flow chart), which will include information on the retention/withdrawal (including timing and reasons) of wards during the evaluation. We will also present the number of health practitioners who completed the questionnaires and interviews against the number of professionals working in the wards during the evaluation, and the number of patients/carers completing the questionnaires/interviews against those discharged during the duration of the study. We will also conduct basic psychometric analyses to verify the scale structure and internal consistency of the used questionnaires. For explorative purposes, we will examine differences between the three measures completed by patients recruited during the baseline phase and the measures completed by the patients during the intervention phase. Before starting with the analyses, we will examine if the data are normally distributed. If the data are normally distributed, parametric tests will be used, otherwise non-parametric tests will be used. The significance level for all analyses will be p≤0.05. The data analyst will be blinded to the phase allocation (baseline or intervention phase).

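### The CTM-4 scoring formula in Table 2 runs from 0 to 300, not the 0–100 stated beside it; a division by 3 is missing from the text

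*Protocol article*

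**What the plan says.** The Quantitative outcomes section lists three patient and carer questionnaires, one of which is "a short four-item version of the CTM". The scoring column of Table 2 gives the response format: "The CTM items are rated on a 4-point Likert scale ranging from 1=‘strongly disagree’ to 4=‘strongly agree". A fifth response covers items that the respondent cannot answer, and it is left out of the score: "The summarised score (excluding the ‘not applicable’ scores". The score itself is "computed as the total sum divided with the number of answered items, minus 1 and multiplied by 100 to get a total score (0–100", per respondent, with higher values meaning a better experience.

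The Data analysis plan then uses the score: "For explorative purposes, we will examine differences between the three measures completed by patients recruited during the baseline phase" and those completed during the intervention phase. The test level is given as "The significance level for all analyses will be p≤0.05".

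**The concern.** The formula and the range stand in the same sentence and cannot both be right. With items coded 1 to 4, subtracting 1 from the item mean moves the floor to 0 but leaves the ceiling at 3. To reach 0–100, the result must also be divided by the item range of 3. That step appears neither in Table 2 nor anywhere else in the article.

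What is at stake is the reporting unit of one of the three patient and carer scales. If someone codes the rule literally, the CTM-4 means, SDs and raw differences come out on a 0–300 scale under a 0–100 label. A reader could not interpret them or set them beside CTM results that really are on 0–100. Anyone who reuses the published formula would repeat the error.

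**Working it through.** **Inputs (all from Table 2 and the Quantitative outcomes text).** Item codes 1, 2, 3, 4; four items; the fifth response excluded from both the sum and the count; stated range 0–100. Let *n* be the number of answered items (1 to 4) and *m* = sum / *n*, so *m* lies between 1 and 4.

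**Trying to reproduce the stated range.** The natural reading is score = (*m* − 1) × 100. The last column adds the division by 3.

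| All answered items at | (*m* − 1) × 100 | (*m* − 1) / 3 × 100 |
|---|---|---|
| 1 | 0 | 0 |
| 2 | 100 | 33.3 |
| 3 | 200 | 66.7 |
| 4 | 300 | 100 |

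The stated range is not reproduced. A respondent who answers 2 throughout already scores the supposed maximum, and any item mean above 2 scores over 100.

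**Other readings of the sentence**, each applied to every response pattern with at least one answered item:

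- sum / (*n* − 1) × 100: 133 to 800, and undefined when only one item is answered. With all four answered it runs from 4/3 × 100 = 133 to 16/3 × 100 = 533.
- sum / *n* − (1 × 100): −99 to −96.
- (sum / *n*) × 100 − 1: 99 to 399.
- ((sum − 1) / *n*) × 100: 0 to 375.

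None gives 0–100. Dividing (*m* − 1) by the item range, 4 − 1 = 3, gives exactly 0 to 100 whatever the number of answered items.

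**What changes and what does not.** Under the natural reading, the score as written is 3 × the 0–100 score for every respondent. Means, SDs and raw differences are therefore multiplied by 3. A standardised difference is a raw difference divided by an SD, so the 3 cancels, as it does in a t statistic. Ranks are unaffected, so rank tests are unchanged. Cronbach's alpha is computed from the items, and completion rates do not use the score.

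An illustration with simulated responses, 45 per phase (the group size in Table 1; the response probabilities are arbitrary):

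| | As written | Divided by 3 |
|---|---|---|
| Baseline mean | 196.1 | 65.4 |
| Baseline SD | 45.8 | 15.3 |
| Difference between phases | 5.0 | 1.67 |
| Standardised difference | 0.113 | 0.113 |
| t-test p | 0.595 | 0.595 |
| Mann–Whitney p | 0.736 | 0.736 |

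**The case against.** The strongest reply is that this is a slip in describing the score, with little depending on it. The same sentence states the intended range, so a dropped division by 3 is the likely explanation. Literal scoring would also produce values above 100, which a simple range check would catch. No scoring code is shown, so there is no evidence that any result will be wrong. The comparison between phases is labelled exploratory. The Discussion says that interest lies mostly in completion rates and that power is too low for meaningful quantitative analysis of these measures. No threshold, progression rule or sample size in the article uses the CTM-4 score. All of this stands, and it keeps the point minor. It does not remove the contradiction: the article commits to a formula and a range that disagree, so this is not detail left to a fuller document.

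A reader might go further and infer that the later trial would be oversized. The Abstract says that the findings will inform how many patients and wards to include, and an SD three times too large, paired with a target difference on 0–100, would multiply the sample size by 3² = 9. The documents do not support that inference. Nothing says that CTM-4 will size the later trial or that its SD will be carried forward. If the SD and the target difference came from the same scale, the factor would cancel.

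The text could also be made consistent by stating the range as 0–300. That is possible, but it would give up the 0–100 scale that the table announces.

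**Conclusion.** The point holds as a minor correction. The CTM-4 formula in Table 2 gives 0–300 and contradicts its own stated 0–100. The threefold inflation of means, SDs and raw differences is conditional: it arises only if the score is computed literally, on the natural reading of the sentence. The tests, standardised effects, internal consistency and completion rates in the plan are unaffected in either case. The conclusion rests only on the 1-to-4 item coding and on the formula as printed, and it needs no outside source on how the measure is scored.

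**What to change.** In the CTM-4 row of Table 2, replace the scoring sentence with: score = ((sum of answered items / number of answered items) − 1) / 3 × 100, range 0–100, with the don't know / don't remember / not applicable response excluded from both the sum and the count. Then confirm that the scoring routine returns 0 when all items are 1 and 100 when all items are 4.

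This costs one line of text and one check of the scoring. It changes nothing in the design, the data collected or the tests planned.
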